# 7. Methods

## 7.1 Routine clinical blood tests

These, taken as part of normal clinical care, will be processed at the Local Laboratories and include (but not exclusively): FBC, UE, Iron Studies, B12, Folate and CRP.

## 7.2 Core laboratory assessments

One single tube (6-8mL or 1.5 teaspoons) will be collected and processed into four to six aliquots at each site (further details can be found in the Manual of Procedures).These will be centralised on block to the research team (Harry Perkins Institute of Medical Research South). Research samples will be stored in a de-identified manner at the study site in a -80 freezer at local sites. They will be shipping in bulk to the central store (Laboratory freezer owned by the [name] research team located at Harry Perkins Institute of Medical Research - South).

Laboratory analyses will include but not exclusively markers of erythrogenesis (EPO, Erythroferrone), markers of iron metabolism (Ferritin, Tsats, sTFR), markers of inflammation (CrP, IL6, IL22), markers of phosphate metabolism (Vit D, FGF23, Phosphate) and phenomic and metabolomic analyses.

For the purpose of this current trial, one de-identified aliquot will be shipped to The [name] Group, Department of Physiology, Anatomy & Genetics, Oxford University, UK for iron metabolism analyses (hepcidin and ferroportin).

Remaining serum and aliquots will be held in the research team -80 freezer for future use. Access to samples for additional analyses will be governed by a trial steering committee comprising the clinical lead investigators and scientific investigators for this study. Where possible and within the constraints of international law and specific requirements of local ethical and institutional management approvals.

## 7.2 Clinical assessments

The time schedule for the assessments and the time windows allowed are provided in the flow chart in Section 6.4 and 6.5. All patients must be followed according to protocol, clinical status permitting, whether they receive their allocated trial treatment or not (unless the patient withdraws their consent for follow-up).

**Clinical frailty score**

Clinical Frailty Scale (CFS) will be used to assess frailty of patients enrolled in the trial. CFS is used to predict health outcomes that are significantly associated with mortality, morbidity, functional decline, mobility, and cognitive decline. It uses a 9-point scale (very fit -severely terminally ill).

## 7.3 Quality of life assessments

**SF-36v2**
SF-36v2 is a health survey that measures the functional health and well-being from the point of view of the patient. It can be used across age, disease, and treatment groups, in contrast to a disease-specific health survey which focuses on a particular disease or condition. Version 2 will be used and is modified for use in Australia.

**European Quality of Life-5 Dimensions-5 Levels (EQ-5D-5L)**The Eq-5D-5L is a brief, utility- based HRQoL instrument. It consists of a health descriptive system and a visual analogue scale (EQ-VAS) for respondents to self-classify and rate their health on the day of administrating of the instrument.

## 7.4 Functional assessments

It is not envisaged that all patients will undergo all these tests at all participating hospital sites. Some sites may be able to undertake a 6MWT and others not. Similarly, this may not be feasible in some patients (vascular). The feasibility to undertake one or all these tests is part of the outcome evaluation of the trial. i.e. what functional tests can routinely and accurately be performed in the post operative and recovery period after surgery?

**Grip Strength**Participants will be assessed using a calibrated JAMAR dynamometer. Each hand will be assessed twice and the greater of the two forces will be recorded and correlated to a rating system (excellent, very good, etc.).

**Six-minute walk test**

Patient will be assessed on a straight 30 metre track that they will lap for 6 minutes to objectively measure their functional ambulatory capacity throughout study. A resting electrocardiogram done during the previous 6 months will be reviewed prior to testing.

**Absolute contraindications:**

1. Unstable angina during the previous month
2. Myocardial infarction during the previous month

**Relative contraindications:**

1. Resting heart rate > 120
2. Systolic blood pressure > 180 mm Hg
3. Diastolic blood pressure > 100 mm Hg

**Sit-to-stand (STS) test**

The sit-to-stand test measures a patient’s leg strength and endurance by having them stand up from a sitting position repeatedly over the course of 30 seconds.

**The Timed Up and Go test (TUG)**

The TUG test measures a patient’s mobility, balance, walking ability and the fall risk. It uses the times a patient standing from a chair with no arms, walking 5 metres and returning to sit down.

##

## 7.5 Criteria for discontinuing or modifying allocated interventions [11b]

Adverse events occurring in connection with the administration of study medication will be recorded. In the event of a participant having an allergic reaction or signs of intolerance during study drug administration, the investigator must immediately stop the study treatment and notify the principal investigator. If the treatment is stopped for other reasons and the patient is willing the treatment can be restarted where possible (as per local practice).

## *7.6* Definition of end of trial

The end of the study is defined as the date that the last patient has completed his/her last study visit, or one year following randomisation of this last patient.

***Premature termination of the entire study***

The sponsor has the right to terminate the study at any time. Reasons which may require termination include the following:

- Recommendation from the DSMC.
- New toxicological or pharmacological findings or serious adverse events invalidate the earlier positive risk-benefit-assessment.
- The incidence and/or severity of adverse events in the study indicate a potential health hazard caused by treatment with the study medication.

## 7.7 Withdrawal of participants

A patient may decide to withdraw from the study at any time without prejudice to their future care. A patient may withdraw from the follow-up visits or they may withdraw their consent for any data collected to be used. Patients will be encouraged to allow data and samples that have been collected before withdrawal to be used in the analyses. However, if consent to use data/samples is also withdrawn, then these will be discarded. Patients withdrawing from the study will continue to be followed-up by their local team.

Patients who have consented and been randomised but do not receive the investigational product will stay on the study and will be followed up as in line with this protocol unless patient consent is withdrawn.

If a patient's treatment was stopped before being fully given for any reason the patient will be followed up as in line with this protocol unless consent is withdrawn.

Patients who withdraw from the trial will not be replaced, but their data will be included based on the intention-to treat principle (unless they withdraw consent for their data to be used).

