# 7. Study Procedures [13]

7.1 Informed consent [26a][26b]

Written informed consent will be obtained prior to performing any trial-specific procedure by the investigator or delegate. Participants must be given written and verbal information, in lay terms, of the aims, methods, anticipated benefits and potential hazards, and given sufficient time to consider whether they wish to participate. The participants must be notified that participation is voluntary, and that they are free to discontinue treatment or withdraw consent from the study at any time without any disadvantages for their future care and treatment. If the participant agrees to participate in the trial, they will be asked to initial, sign and date the latest version of the Participant Information Consent Form (PICF). The Investigator or delegate will then sign and date the form. A copy of the PICF will be given to the participant, a copy will be filed in the medical notes.

Patients will be invited at the time of study enrolment to provide optional written informed consent for donation of blood sample for future biological or translational sub-studies
for future research use, pending relevant ethics and governance approval.

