### 7.2.3 Unblinding [17b]

Treatment unblinding will only occur when there are legitimate clinical concerns where the appropriate management of the participant necessitates knowledge of the treatment allocation. All cases of emergency unblinding will be thoroughly documented and reported to the data safety monitoring board (DSMB). After all participants have completed the study, participants will be notified which arm of the study they took part in.

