## 11.4 Statistical Analysis [20a]

Analyses will be based on all randomised participants. Reporting of research findings will be in accordance with CONSORT guidelines. Baseline demographic data and other participant characteristics will be expressed as means and standard deviations for continuous variables and counts and percentages for categorical variables, with 95% confidence intervals provided for estimates of interest where appropriate. The differences in baseline characteristics will be evaluated by either $\chi^{2}$ or Fisher extract test for categorical variables and an independent samples t-test for continuous variables. Changes in recovery outcome scores will be compared for each participant as the difference between baseline and each specified time points scores with univariate analyses comparing changes in outcome.

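### Section 7.7 discards all data when data consent is withdrawn, with no exception for adverse events, exposure or allocation already recorded, and section 7.2.3 does not place allocation notices after database lock

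*Protocol*

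**What the plan says.** Section 7.1 tells participants that "they are free to discontinue treatment or withdraw consent from the study at any time". Section 7.7 sets out two kinds of withdrawal: "A patient may withdraw from the follow-up visits or they may withdraw their consent for any data collected to be used". For the second kind it states the consequence: "However, if consent to use data/samples is also withdrawn, then these will be discarded". The only restraint is persuasion: "Patients will be encouraged to allow data and samples that have been collected before withdrawal to be used in the analyses". The same section carries the exception into the analysis set, where for those who withdraw "their data will be included based on the intention-to treat principle (unless they withdraw consent for their data to be used").

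Section 7.5 covers stopped dosing, beginning "In the event of a participant having an allergic reaction or signs of intolerance during study drug administration". Section 7.2.3 deals with telling participants their arm: "After all participants have completed the study, participants will be notified which arm of the study they took part in". Section 11.4 defines the analysis set: "Analyses will be based on all randomised participants".

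Four other places bear on the point. Section 9.1 commits the trial to recording and reporting every adverse event. Section 7.6 (premature termination) lists the incidence and severity of adverse events among the reasons to stop the study. Section 14.2 sends serious adverse events to the regulators. Sections 10.2 and 14.5 require case report forms and trial documents to be kept for 15 years, or in section 14.5 for the period set by regulation.

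**The concern.** Withdrawal of data consent is seldom random. A participant who reacted during the infusion has an obvious reason to want nothing more to do with the study, and needs no unblinding to act on it. If everything recorded on that person is then discarded, the trial loses both the reaction and the fact that the person was exposed. Section 8.2 makes the comparator normal saline, so reactions to the study drug arise in the iron arm and their loss would be unequal between arms. The reported reaction rate, and the incidence available to the safety committee, would then be too low.

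The timing of allocation notices is a second and weaker route. If participants learn their arm while data can still be removed, removal can depend on the arm. With 20 patients per arm in each surgical cohort, a few such removals would be visible in the cohort results.

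**Working it through.** **Passages side by side**

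| Question | What the protocol gives |
|---|---|
| Can data already collected be withdrawn? | Yes (7.7) |
| What happens to them? | Discarded (7.7) |
| Is there a last date for this? | None stated |
| Are adverse event, exposure or allocation data exempt? | No exemption stated |
| Are discards counted by arm? | Not stated |
| When may participants learn their arm? | Once all have completed (7.2.3); database lock is not mentioned anywhere |
| Must every adverse event be reported? | Yes (9.1) |

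The rule in 7.7 and the rule in 9.1 cannot both be followed for a participant who had an adverse event and then withdraws data consent. This rests on 7.7 alone and does not depend on when allocation is disclosed.

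**Arm sizes (section 11.2)**

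2 groups × 3 cohorts × (20 + 20) = 240, which reproduces the stated total. The iron arm is 20 per cohort, 60 per group and 120 overall. One discarded patient is 1/20 = 5% of a cohort arm.

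**Reaction counts**

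The protocol gives neither a reaction rate nor a rate of data withdrawal for this trial, so both are assumed here.

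- 3 of 120 = 2.5%. After one discard: 2 of 119 = 1.7%, about a third lower.
- 6 of 120 = 5.0%. After three discards: 3 of 117 = 2.6%, about half.

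**Haemoglobin, worst case**

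Suppose the k lowest values in one arm of size n are discarded and values are normal. With f = k/n, the arm mean shifts by SD × φ(z_f)/(1 − f).

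The protocol states no SD. For a range, the Background section reports a haemoglobin difference of 10.7 g/L (95% CI 7.8 to 13.7) in the earlier preoperative trial of 487 patients. The standard error is (13.7 − 7.8)/(2 × 1.96) = 1.51. If all 487 were analysed in equal arms, the SD is 1.51 × √487/2 = 16.6 g/L. A range of 12 to 17 g/L is assumed.

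| Discarded | Shift in SD | Shift in g/L |
|---|---|---|
| 1 of 20 (cohort arm) | 0.11 | 1.3 to 1.9 |
| 2 of 20 (cohort arm) | 0.20 | 2.3 to 3.3 |
| 1 of 60 (group arm) | 0.04 | 0.5 to 0.7 |
| 3 of 120 (whole arm) | 0.06 | 0.7 to 1.0 |

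These are upper bounds, because they assume that exactly the lowest values go and all from one arm. Against 10.7 g/L, the whole-arm figure is small. The cohort figures are not negligible.

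**The case against.** The case against is substantial, and several stronger readings fail.

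- **Disclosure before lock.** A reader might infer that participants will be told their arm before the database is locked. Section 7.2.3 sets only an earliest point, and notification after lock complies with it in full. It also requires all participants to have finished, not just the person concerned. What stands is that the order is left open. Nor does the section say who gives the notice or whether data queries would still be open, so a claim that site staff would be unblinded too early has no support.
- **Conflict with the analysis set.** A reader might set 7.7 against the all-randomised analysis in 11.4. Section 7.7 states its own exception for withdrawn data consent, and a general rule with an express exception is not a contradiction.
- **Erasure from every record.** A reader might infer that a reaction vanishes altogether. Section 7.5 requires events connected with administration to be recorded and the principal investigator to be notified, section 14.2 sends serious events to regulators, and sections 10.2 and 14.5 require records to be kept. The word discarded may also have been meant only for use in the analyses. These soften the point, but none says that adverse event data stay in the trial's reported data once data consent is withdrawn.
- **The consent form.** It is not in the material at hand and may limit data withdrawal. If so, 7.7 should say the same.
- **Legitimacy.** Letting participants withdraw collected data is a proper consent choice and not an error. How far data may be kept against a participant's wish depends on Australian and UK rules that the protocol does not set out.

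**Conclusion.** The point holds in a limited form. Section 7.7 lays down a discard rule without a safety exception, and this does not fit the commitment in 9.1 or the reliance on adverse event incidence in 7.6. Losses after a reaction would fall mainly in the iron arm. Allocation-dependent deletion is a gap in 7.2.3, not something the protocol prescribes.

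The size is unknown, because no frequency of full data withdrawal is given; it is probably low. On assumed counts, one discard lowers a reaction rate from 2.5% to 1.7%. For haemoglobin, the worst case over a whole arm of 120 with three discards is 0.7 to 1.0 g/L, on an assumed SD of 12 to 17 g/L, so the main comparison is unlikely to change. The sensitive parts are reaction counts and the cohorts with 20 per arm. The change is worth making because it is cheap and discarded data cannot be recovered at the analysis stage.

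**What to change.** In section 7.7, state three things:

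1. Randomisation, allocation, exposure and AE/SAE data recorded before withdrawal are kept for safety reporting and participant flow, as far as law, ethics approval and the consent form allow.
2. Efficacy and quality-of-life data and stored samples may be discarded on request up to database lock.
3. The number of full data withdrawals is reported by arm.

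In section 7.2.3, state that participants are told their allocation only after database lock.

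The cost is an amendment to the protocol and consent wording, with ethics review. Participants could no longer have safety records erased, and would learn their allocation slightly later. Sample size, visits and procedures do not change.

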## 7.8 Relevant Concomitant Care Permitted or Prohibited During the Trial [11d]

During the trial, the study team will ask participants to continue their normal activities, in particular:

1. Avoid major changes to diet and or diet manipulation strategies
2. Avoid iron supplementation

All medications being continued by a patient on enrolment and all medications given in addition to the study medication during the study are regarded as concomitant medications and will be documented by the patients in the patient diaries (these details will be transcribed into the eCRF), and in the patient’s medical records. All changes to concomitant medication taken from enrolment until completion of the study will also be recorded (including changes in dose, change in formulation, starting or stopping medication).

## 7.9 Post-trial care arrangements [30]

There will be no post-trial treatment arrangements as the treatment is a single dose. At completion of the study, participants will continue clinical follow up as necessary or be discharged from clinical follow up as per standard of care, this decision will be made by their usual clinician.

# 8. Investigational Product [11a]

8.1 Description of Investigational Product
The investigational product is intravenous iron preparation. Ferric carboxymaltose (Ferrinject) or iron isomaltoside (Monofer®) will be used as per local practice. For further information please refer to the summary of product characteristics.

### 8.1.1 Summary of known and potential risks and benefits

The side effects of the intravenous iron are minimal: the common side effects (>=1/100, <1/10) are headache, dizziness, hypertension, nausea, alanine aminotransferase increased, hypophosphataemia and injection site reactions, as detailed in the summary of product characteristics.

## 8.2 Placebo

Medication name: NaCl (normal saline)

Trade name: NaCl

Active ingredient: NaCl (normal saline)

Dosage form: 0.9% w/v NaCl as sterile solution in water for injection

Excipients: Water

Strength/Packaging: 100 mL container with 100 mL normal saline

Manufacturer: As per local hospital supplier

## 8.3 Route of administration and dosage

IV administration of trial drug will be given by slow IV push (Ferrinject®) or infusion over 15 - 30 minutes (Monofer®). Administration will be given in accordance with local practice for the use of intravenous iron.

Participants should be closely monitored as per local hospital standard care protocol throughout administration of the treatment.

## 8.4 Preparation and labelling of Investigational Product

Packages of investigational product will be labelled with storage conditions (store below 30°C), batch number and expiry date, as per the manufacturer. Labelling of the investigational product will comply with Therapeutic Goods Administration (TGA) code of Good Manufacturing Practice (GMP) for investigational products, Annex 13, section 17 in Australia, or applicable national and/or local requirements for international sites.

## 8.5 Handling and Storage of Investigational Product

Investigational product will be stored below 30°C until use in accordance with manufacturer’s instructions. The site investigator or delegate must maintain an adequate record regarding the administration of all investigational product within the trial. Accountability documentation will also reside with the site investigator and be retained in the Trial Master File at the coordinating centre.

# 9. Safety reporting [22]

9.1 Adverse Event (AE)

An AE is any untoward medical occurrence in a patient temporarily associated with the use of a medicinal product, whether or not considered related to the medicinal product. An AE can therefore be any unfavourable and unintended sign (including an abnormal laboratory finding), symptom, or disease (new or exacerbated) temporally associated with the use of a medicinal product, whether or not considered related to this medicinal product.

All adverse events will be captured and reported as per the CONSORT guidelines. Detailed description can be found in the procedures manual.

9.2 Serious Adverse Event (SAE) 
A SAE is any untoward medical occurrence that at any dose:

- Results in death,
- Is life-threatening,
- Requires hospitalisation or prolongation of existing hospitalisation,
- Results in disability/ incapacity,
- Congenital anomaly/birth defect,
- Other important medical events which, in the opinion of the investigator, are likely to become serious if untreated, or as defined in the protocol

## 9.3 Suspected Unexpected Serious Adverse Reaction (SUSAR)

A SUSAR is any SAE that is both suspected to be related to the study treatment and is unexpected (i.e., not consistent with applicable product information).

## 9.4 Pregnancy

Should a participant become pregnant whilst undertaking the trial, the pregnancy and resulting child will be followed up for a period of no less than 12 months.

# 10. Data Management [18a]

## 10.1 Case Report Form

A Case Report Form (CRF) will be completed for each participant. Participants will be referred to in the CRF by their initials, study number and the date of the visit for identification. All participating hospital sites must store any paper-based forms in accordance with GCP guidelines.

## 10.2 Data management [19]

Data will be recorded in an electronic CRF. The AMBLE Research Electronic Data Capture (REDCap) database is hosted on by Fiona Stanley Hospital, South Metropolitan Health Services behind a firewall with two factor authentication for administrators using a modern web browser. Access to the database at each participating hospital site will be secure and password protected and managed by the Data Manager. Access to the REDCap database at each participating hospital site will be granted after documented training. All information collected on the eCRF will have identifying information removed.

All original CRF will be securely archived at the participating hospital site for a minimum of 15 years and in accordance with applicable legislation.

Data will be extracted from the system by exporting the database table as CSV text files or another suitable format. Analyses will be conducted by the trial statistician in a statistical package (such as STATA) after importing the database tables. For unblinded analyses these files may be combined with the CSV file exported form the unblinded randomisation system.

